#### Pain Disability Index

The Pain Disability Index (PDI)^58^ measures the extent to which pain affected the participants’ ability to function in various areas of life. Participants will rate their level of pain disability on a 10-point Likert scale from 0 (‘no disability’) to 10 (‘total disability’) across seven life domains. A total score for pain disability will be calculated as the sum of all item ratings. The PDI will be assessed at two time points (visits 0 and 9).

#### Perceived Stress Scale

As part of the Perceived Stress Scale (PSS),^59^ patients will be asked to rate the frequency of stress-related thoughts and feelings over the past month on a 6-point Likert scale from 0 (‘never’) to 5 (‘very often’). A total score for perceived stress will be calculated as the sum of the individual values across all items. The PSS will be assessed once at visit 0.

#### Somatosensory Amplification Scale

Patients will rate their increased sensitivity to bodily sensations using the Somatosensory Amplification Scale (SSAS)^60^ on a 5-point-Likert scale from 1 (‘completely’) to 5 (‘not at all’). An overall score will be calculated by summing the individual values across all items. The SSAS will be assessed once at visit 0.

#### State-Trait Anxiety Depression Inventory-state

State anxiety and state depression will be assessed using the State-Trait Anxiety Depression Inventory (STADI-state).^61^ Patients will be instructed to rate the intensity of their current anxiety and depression symptoms on a 4-point Likert scale from 1 (‘not at all’) to 4 (‘very much’). An overall score will be calculated as the sum of the individual values across all items. The STADI-state will be measured at nine time points (visits 1–9).

#### STADI-trait

Trait anxiety and trait depression will be assessed using the STADI-trait.^61^ Patients will be instructed to rate the frequency of anxiety and depression-related symptoms on a 4-point Likert scale from 1 (‘rarely’) to 4 (‘very often’). An overall score will be calculated as the sum of the individual values across all items. The STADI-trait will be measured once at visit 0.

#### Substance use assessment

Substance use will be assessed using a questionnaire that captures the frequency and quantity of alcohol, nicotine and caffeine consumption over the past 7 days. Specifically, patients will be asked: ‘On how many days and in what quantity have you consumed one of the following substances in the past week?’ (German: ‘An wie vielen Tagen und in welcher Menge haben Sie in der vergangenen Woche eine der folgenden Substanzen konsumiert?’). For each substance, patients will be asked to indicate the number of days on which they had consumed the substance during the past week and the total number of units consumed during that time frame. A standardised unit definition will be provided: one unit of alcohol will be defined as 0.33 L of beer, 0.15 L of wine or 0.04 L of spirits. One unit of cigarettes will be defined as one cigarette, and one unit of caffeine will be defined as one cup of coffee, black or green tea or 0.5 L of coca cola.

In addition, patients will have the option to report any further psychoactive substances they had used within the time frame. Substance use will be assessed once at visit 1.

#### Treatment Expectation Questionnaire

To assess various dimensions of treatment expectations, patients will rate items from the Treatment Expectation Questionnaire (TEX-Q)^62^ using a VAS ranging from 0 (‘none’) to 10 (‘greatest imaginable’). An overall treatment expectation score will be calculated by averaging the ratings across all items. To assess specific dimensions of treatment expectation (eg, probability, valence and outcome), a sum score will be computed for each subscale. The TEX-Q will be assessed once at visit 1.

#### Warmth and competence

To assess the perceived warmth and competence of the treating physician, patients will rate items of the Warmth and Competence Scales of the Stereotype Content Model^63^ on a 5-point-Likert scale from 1 (‘not at all’) to 5 (‘extremely’). Mean scores for subscales will be calculated. Warmth and competence will be assessed once at visit 9.

### Sample size, group allocation and blinding

#### Sample size

To test the non-inferiority of the drug-dose reduction strategy to the standard care at an exploratory level, the sample size calculation was conducted in R using the epiR package (function: epi.ssninfb). This calculation is based on a non-inferiority framework using the absolute risk difference scale. For the purpose of calculation, a favourable outcome was assumed for 70% of participants in the reinforcement group and 75% in the TAU group. The non-inferiority margin was set to an absolute risk difference of 0.25, corresponding to a minimal clinically important difference (MCID) of >25%. Assuming a one-sided α=0.05 and 80% power, a total sample size of N=152 was required for a 1:1 comparison between TAU and the pooled reinforcement groups. As the primary non-inferiority hypothesis compares TAU with the pooled reinforcement groups, the sample size calculation was based on a 1:1 allocation ratio.

To account for the dropout rate of 10% during a previous study, which investigated the impact of verbal inductions of positive treatment-related expectations as a dose-reduction strategy in patients with psoriasis,^33^ a sample size of N=168 is set.

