### Analysis plan

All statistical analyses will be conducted using R^64^ (V.4.1.1.; R Core Team, Vienna, Austria) within RStudio^65^ (RStudio Team, Boston, MA).

Confirmatory hypotheses will be tested using linear mixed models, assuming approximate normality of random effects and residuals. If model diagnostics indicate substantial violations of distributional assumptions, generalised linear mixed models with appropriate link functions and distribution will be applied based on the observed characteristics of the data.

Each model will include Group as a between-subject factor and Time (10 levels, one per visit) as a within-subject factor. The Group factor represents the treatment conditions (TAU, partial reinforcement and continuous reinforcement). The number of Group levels varies by hypothesis and will be specified within each hypothesis section. Random intercepts for participants will be included to account for individual differences. Random slopes will be added if they significantly improve model fit, as evaluated by likelihood ratio tests and information criteria (ie, Akaike Information Criterion, Bayesian Information Criterion).

Main effects and Group × Time interactions will be examined depending on the respective hypotheses. Pairwise comparisons of estimated marginal means will be conducted where appropriate, with Holm-adjusted p values used to control for multiple comparisons, particularly given the unbalanced group sizes. A significance level of α=0.05 will be applied for all confirmatory tests.

#### Hypothesis 1

We hypothesise that both experimental treatments (pooled across partial and continuous reinforcement) will be non-inferior to the TAU group regarding average reductions in itch, PASI and DLQI scores from pre-measurement to post-measurement. Non-inferiority testing will be embedded within the linear mixed model framework. One-sided 95% CIs will be computed based on model estimates. Non-inferiority will be concluded if the upper bound of the CI lies below the predefined MCID of 25%.^66^

#### Hypothesis 2

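### The stated 80% power is calculated for a risk difference, but Hypothesis 1 tests mean score reductions, so the power of the planned non-inferiority test is unsupported

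*Protocol article*

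**What the plan says.** The Sample size section of the protocol article sets the scale: "This calculation is based on a non-inferiority framework using the absolute risk difference scale". The assumed rates follow: "a favourable outcome was assumed for 70% of participants in the reinforcement group and 75% in the TAU group". The margin is then tied to a clinical threshold: "The non-inferiority margin was set to an absolute risk difference of 0.25, corresponding to a minimal clinically important difference (MCID) of >25" per cent. The result is given as "Assuming a one-sided α=0.05 and 80% power, a total sample size of N=152 was required for a 1:1 comparison" of TAU with the two reinforcement groups pooled. The total is raised to 168, "To account for the dropout rate of 10% during a previous study".

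The Analysis plan, under Hypothesis 1, states a different kind of test. The pooled reinforcement groups "will be non-inferior to the TAU group regarding average reductions in itch, PASI and DLQI scores from pre-measurement to post-measurement". On method: "Non-inferiority testing will be embedded within the linear mixed model framework". A one-sided 95% confidence bound is compared with an MCID of 25%, with no scale or reference value attached. Hypotheses 2 to 4 also model scores or trajectories. Neither the listed outcomes nor the exploratory analyses include a responder proportion. The generalised mixed model is only a fallback if the distributional assumptions fail.

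**The concern.** The sample size section and the analysis plan describe the same comparison (TAU against pooled reinforcement) on two different scales. The power of a risk-difference test depends on two response rates and a margin in absolute risk. The power of a test on mean reductions depends on the SD of change, the true mean difference and a margin in score units, and none of these enters the calculation. The only link is the statement that a risk difference of 0.25 corresponds to an MCID of 25%. That link cannot be made without a responder threshold and a score distribution, and the article gives neither.

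What is at stake is how the result is read. If the power of the planned test is unknown, a failure to show non-inferiority may have been likely from the start, or a pass may have been close to guaranteed. The reader cannot tell which. The Type I error rate of the test itself is not affected.

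**Working it through.** **Step 1: reproduce the plan's own figure.** Inputs from the Sample size section: rates 0.75 (TAU) and 0.70 (reinforcement), margin 0.25, one-sided α = 0.05, power 80%, allocation 1:1.

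- Distance from the true difference to the margin: 0.25 − (0.75 − 0.70) = 0.20.
- Sum of variances: 0.75×0.25 + 0.70×0.30 = 0.1875 + 0.2100 = 0.3975.
- n per group = 0.3975 × (1.645 + 0.842)² / 0.20² = 0.3975 × 6.18 / 0.04 = 61.4, so 62 per group and **124 in total, not 152**.
- Power at 76 per group: SE = √(0.3975/76) = 0.0723, and Φ(0.20/0.0723 − 1.645) = Φ(1.12) = **87%**.

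Variants at one-sided 0.05 do not reach 152 either: pooled variance 124, null-restricted variance 122, continuity correction 144, 2:1 allocation 138 to 141. One-sided 0.025 gives 154 (null-restricted) or 156 (unpooled), and a margin of 0.23 gives exactly 152. Neither that α nor that margin is the stated one.

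The dropout step is not the problem: 152 × 1.1 = 167.2, so 168, against 152/0.9 = 168.9, so 169. The difference is one patient. With 10% dropout, 168 leaves 168 × 0.9 = 151 evaluable.

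**Step 2: power for a test on means.** Assumption: a simple two-group comparison of change, with equal SDs and a normal approximation. The repeated-measures model may be somewhat more precise, depending on within-patient correlations that the article does not give.

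- SE of the difference = SD × √(2/76) = 0.162 SD.
- 80% power requires (margin − true difference)/SD = (1.645 + 0.842) × 0.162 = **0.403**.
- In general, power = Φ(ratio/0.162 − 1.645), where ratio = (margin − true difference)/SD.

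| Ratio | Power at 76 per group | Total N for 80% |
|---|---|---|
| 0.20 | 34% | 620 |
| 0.30 | 58% | 276 |
| 0.40 | 79% | 156 |
| 0.50 | 92.5% | 100 |
| 0.60 | 98% | 70 |

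**Step 3: can the ratio be read from the article?** No. It states no SD of change, no expected mean difference and no margin in score units. As an illustration only, assume that the 25% means 25 percentage points of percentage reduction and that the true difference is 5 points. Power at N=152 is then 92.5%, 79%, 66% and 46% for SDs of 40, 50, 60 and 80 points. These inputs are assumptions and do not come from the article.

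**The case against.** The strongest defence is that sizing on a dichotomy is usually conservative, because a continuous analysis of the same outcome uses more information. Suppose a favourable outcome were a cut on a normally distributed change score with equal SDs in both groups. Rates of 75% and 70%, with a non-inferiority limit at 75% − 25% = 50%, correspond to normal quantiles 0.674, 0.524 and 0. The distance from true value to limit is then 0.524 SD, and power on means at 76 per group is Φ(0.524/0.162 − 1.645), about 94%. This argument stands as a possibility. It does not rescue the text, because the article does not state that construction and its limit for Hypothesis 1 is a bare 25%, not a limit derived from a responder cut. It does show that the mismatch need not work against the sponsor.

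The Sample size section also says that non-inferiority is tested at an exploratory level. That qualifier matters but does not resolve the conflict: the same section calls this comparison the primary non-inferiority hypothesis, and the Analysis plan introduces its mixed models as tests of confirmatory hypotheses.

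The definition of a favourable outcome may sit in a fuller document that is not shown. That is fair, so the point does not rest on a missing definition. It rests on the printed conflict between the scale used for sizing and the scale used for testing.

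**Conclusion.** The 80% power is not supported for Hypothesis 1 as the article describes it, because it was calculated for a different quantity. On means, with 76 per group and one-sided 5%, power is 80% only at a ratio of about 0.40, and it runs from about 34% to 98% over ratios of 0.20 to 0.60. This rests on the simple two-group approximation. The ratio itself cannot be derived from anything printed.

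Three stronger readings are tempting and should be resisted:

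- A reader might infer that the trial is underpowered, or that the planned test cannot have 80% power. The article does not show this: the power is undetermined and may lie on either side of 80%.
- A reader might infer that 80% and N=152 are at least right for the risk difference. They are not: the printed inputs give 124, or about 87% power at 152.
- A reader might infer that N=168 is too small. Nothing in the article establishes that.

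**What to change.** Keep N=168 and restate the power for the test that will be run, separately for itch, DLQI and PASI. For each outcome, state a margin in score units, the expected true difference, and the SD of change, with one-sided 5% and about 151 evaluable patients. The Introduction describes the group's own earlier 120-patient secukinumab trial in psoriasis, which is the natural source for the SDs. Delete the statement that a risk difference of 0.25 corresponds to an MCID of 25% on mean scores. Correct the derivation of 152, or withdraw it.

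Replacing the Hypothesis 1 test with a responder analysis, so that it matches the sample size text, is not recommended. Recruitment began on 13 December 2024, and that would be a debatable amendment to the primary analysis.

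The cost is one recalculation, if the SDs can be taken from the earlier trial, and a revised paragraph, with no extra patients. The downside is that the restated power may be less favourable for some outcomes.

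### The printed inputs (70% v 75%, margin 0.25, one-sided 5%, 80% power, 1:1) require N=124, not N=152, so the sample size, the power or an input is misreported

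*Protocol article*

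**What the plan says.** All the inputs stand in the Sample size section of the protocol article, which names the R function used (epi.ssninfb in epiR).

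- Scale: "This calculation is based on a non-inferiority framework using the absolute risk difference scale".
- Rates: "a favourable outcome was assumed for 70% of participants in the reinforcement group and 75% in the TAU group".
- Margin: "The non-inferiority margin was set to an absolute risk difference of 0.25".
- Error rates and result: "Assuming a one-sided α=0.05 and 80% power, a total sample size of N=152 was required for a 1:1 comparison", the two sides being TAU and the pooled reinforcement groups.
- Allocation: "the sample size calculation was based on a 1:1 allocation ratio".
- Dropout: the total is then raised to 168, introduced by "To account for the dropout rate of 10% during a previous study".

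The Analysis plan, under Hypothesis 1, uses the same error rate: "One-sided 95% CIs will be computed based on model estimates". It also uses 25% as the non-inferiority bound.

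**The concern.** A non-inferiority sample size for two proportions is fixed once the two rates, margin, alpha, power and allocation are fixed. All six are printed, so 152 should be reproducible, and it is not. Either the total is wrong for these inputs, or at least one printed input is not the one used.

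Which of these applies matters, because the possibilities describe different designs. Different response rates would mean that the assumption about full-dose treatment given to readers is wrong. A different margin would change the non-inferiority criterion, which Hypothesis 1 also uses. A different alpha would put the design at odds with the one-sided 95% confidence intervals in the Analysis plan. If all the inputs are right, the stated 80% power is wrong. The figure carries forward into N=168 in the abstract and n=84 for TAU.

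**Working it through.** **Inputs (Sample size section):** p(TAU) = 0.75; p(reinforcement, pooled) = 0.70; margin = 0.25; one-sided alpha = 0.05, z = 1.6449; power = 0.80, z = 0.8416; 1:1 allocation.

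**Attempt to reproduce 152.** With unpooled variance:

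n per group = [p₁(1−p₁) + p₂(1−p₂)] × (z₁₋α + z₁₋β)² / (margin − true difference)²

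- Variance term: 0.75×0.25 + 0.70×0.30 = 0.1875 + 0.2100 = 0.3975
- (1.6449 + 0.8416)² = 6.1826
- (0.25 − 0.05)² = 0.04
- n = 0.3975 × 6.1826 / 0.04 = 61.44, so 62 per group and **124 in total**

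The printed total is 152 (76 per group). The excess is 152 − 124 = 28, and 28/124 = 23%.

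**Is it the choice of method or setting?** Rates of 70% v 75% and margin 0.25 unless noted:

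| Variant | Total N |
|---|---|
| Unpooled variance, one-sided 0.05, 80% power | 124 |
| Pooled variance | 124 |
| Farrington-Manning | 122 |
| Continuity correction | 144 |
| Equal rates, 70% / 70% | 84 |
| Equal rates, 75% / 75% | 76 |
| Sign of the difference reversed | 56 |
| Power 85% | 144 |
| Power 90% | 172 |
| One-sided alpha 0.025, unpooled | 156 |
| One-sided alpha 0.025, Farrington-Manning | 154 |

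None gives 152. The closest are the two rows that change alpha to 0.025.

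**Which inputs do give 152?** Working backwards with the same formula:

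- 55% v 60%, all else as printed: (0.2475 + 0.2400) × 6.1826 / 0.04 = 75.35, so 76 per group.
- 70% v 75% with margin 0.23: 0.3975 × 6.1826 / 0.18² = 75.85, so 76 per group. The margin that gives exactly 76 is 0.2298.
- 40% v 45% with margin 0.25 also gives 75.35, and 50% v 60% with margin 0.30 gives 75.74.
- With rates and margin as printed, the alpha that gives 80% power at 76 per group is 0.027.

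The answer is not unique, so the true inputs cannot be recovered from the total.

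**Power of the printed size.** Power = Φ(0.20 / √(0.3975/n) − z₁₋α):

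| n per group | Total | One-sided 0.05 | One-sided 0.025 |
|---|---|---|---|
| 62 | 124 | 80.3% | 70.5% |
| 75.5 | 151 (168 × 0.9) | 86.7% | 78.7% |
| 76 | 152 | 86.9% | 79.0% |
| 84 | 168 | 89.7% | 82.8% |

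Exact binomial power of the Wald test at one-sided 0.05 is 80.8% with 62 per group and 87.2% with 76, so the normal approximation is not the cause.

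**Dropout step.** 124/0.9 = 137.8, so 138, compared with the planned 168. The step from 152 to 168 is a separate and trivial matter: 152 × 1.1 = 167.2 gives 168, and 152/0.9 = 168.9 gives 169.

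**The case against.** The strongest reply is that the error does no harm. On the printed assumptions the trial has about 87% power rather than 80%, the remedy leaves enrolment alone, and the section itself describes the non-inferiority test as exploratory. The direction is indeed conservative, and nothing here suggests that the trial is too small on those assumptions. That limits the consequence but does not make the paragraph correct. The same section also calls this the primary non-inferiority hypothesis, and it is the only basis given for the trial's size.

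A second reply is that the calculation probably used one-sided 0.025. That is the nearest single change of a conventional setting that keeps the printed rates and margin, and 76 per group has 79.0% power there. It should be the first thing checked. It remains unproven: the formula gives 156 and Farrington-Manning 154, and both the Sample size section and the Analysis plan state the 5% one-sided level.

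Third, 55% v 60% and a margin of 0.23 are back-solved values without support in the text. That is right, and they serve only as examples of what would produce 152.

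Finally, 87% is the power of a binary responder comparison, whereas Hypothesis 1 will be tested with linear mixed models on itch, PASI and DLQI scores. This also stands. The printed 80% has the same limitation, so any corrected figure should be labelled as power for the binary sizing model.

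**Conclusion.** The concern holds. The printed inputs require 62 per group, N=124. The stated N=152 is 28 patients (23%) above that and has 86.9% power, not 80%. At least one figure in the paragraph is not the one used, and the document does not allow a reader to say which. The conclusion rests on the standard normal-approximation formula for a risk difference, with the pooled, Farrington-Manning, continuity-corrected and exact checks agreeing that 152 does not follow at the stated alpha and power. If the printed inputs are right, the trial is oversized for this comparison and its power is not at risk. If an input is misprinted, the published design rationale is wrong on that point.

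**What to change.** Re-run the epi.ssninfb calculation, compare it with the original call, and correct the Sample size paragraph. Leave enrolment at 168.

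- **If the printed inputs were used:** state that 124 patients are required (138 after 10% dropout). State also that 168 enrolled, about 151 evaluable, give about 87% power for the binary sizing comparison at one-sided 0.05.
- **If other inputs were used:** print them with the reason, checking alpha first, then the rates and the margin. If alpha was one-sided 0.025, reconcile the one-sided 95% confidence interval under Hypothesis 1 with it. If the margin was not 0.25, reconcile the 25% bound there.

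In either case, print the full function call so that the total can be reproduced. The cost is one corrected paragraph, plus one matching sentence in the Analysis plan if alpha or the margin changes.

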#### Group allocation

The allocation of patients to the study groups will take place after enrolment and receipt of written informed consent. To balance disease severity between groups, the randomisation of patients will follow a stratified randomisation schedule based on PASI scores and will be carried out by the research assistant. The stratified randomisation schedule will be generated prior to study initiation by a postdoctoral researcher who is not involved in patient care, recruitment or data collection. The study physician will have no access to the randomisation list. Prior to recruitment, two strata were established based on PASI scores: 60% of patients were expected to have a PASI ≤15 and 40% a PASI of >15. Within each stratum, randomisation to one of the three intervention groups will be performed using computer-generated random numbers. These numbers will be generated using an Excel spreadsheet and will determine the respective group assignments. To ensure blinding, the group assignment will be initially blackened out, with the group only revealed after the assignment has been completed.

